**Institutional Review Board**

**Intervention/Interaction Detailed Protocol**

Principal Investigator: [name], MPH

Project Title: Time-limited Trials in the Emergency Department: A Randomized Trial

Version Date: 2023.08.16

Version Name/Number: Version 1

1. **BACKGROUND AND SIGNIFICANCE**

In the U.S., approximately 87 older adults (≥ 65 years) require intensive care in emergency departments (ED) every hour.^1^ This often occurs without patients understanding the high risk for newly acquired disability.^2^ During the last six months of life, 75% of older adults visit the ED,^3^ and intensive care is started in 30% of these patients.^4^ Intensive care use in this population increased from 18.5% in 1993 to 24.7% in 2002,^5^ resulting in an annual healthcare expenditure of $108 billion (2010, 4.1% of national healthcare expenditure).^6^ Shared decision-making plays a key role in this population, with more than 70% of older adults reporting that at the end of life, they prefer to focus on quality of life rather than life extension^7^ and would even give up one year of life to avoid dying in the intensive care unit (ICU).^8^ Despite a strong preference against invasive interventions, a systematic review revealed that 56% to 99% do not have advance directives at the time of an ED visit,^9^ reducing the likelihood of successful shared decision-making for initiation of intensive care. Since the decision to initiate intensive care occurs in the ED, emergency clinicians recognize the opportunity to provide patient-centered care.^10^ However, in the time-pressured ED environment, no standardized methods exist to guide emergency clinicians in leading critical shared decision-making regarding initiating intensive care.^11-13^

Experts agree that serious illness care should focus on preparing people for and then supporting them in in-the-moment decision-making during clinical deterioration.^14-16^ Medical crises exemplify the most challenging, in-the-moment decision-making. During medical crises, **time-limited trials (TLT)** are a recommended approach to reducing potentially nonbeneficial treatments for seriously ill older adults.^17-19^ TLT is a structured conversation between clinicians and patients/surrogates to discuss patients’ values and preferences, prognosis, and shared decision-making to use specific therapies for a prespecified period of time. TLT allows both clinicians and patients/surrogates to regularly assess if therapies are meeting patients’ goals over structured time intervals. Guided by the Capacity, Opportunity, Motivation to perform a Behavior (COM-B) framework,^20^ a quality improvement study of TLT in the ICU (N=209) was associated with a 35% increase in formal family meetings (p<0.01), 45% increase in clinicians eliciting values and preferences of patients (p<0.01), 1.3 day decrease in median ICU length of stay (p<0.02), and 13% decrease in mechanical ventilation (p=0.02). No change in hospital mortality was observed (58.4% vs. 58.3%, p=0.99).^21, 22^ TLTs have been published as an expert recommended approach in the official journal of the American College of Emergency Medicine.^23^ Although decisions to initiate intensive care occur in the ED, no study has evaluated the effect of TLT initiated in the ED.

The objective is to assess the feasibility and acceptability of TLT initiated in the ED. We will conduct a pilot randomized trial of TLT on seriously ill older adults starting intensive care in the ED. Rationale: Initiating TLT at the first moment of starting intensive care in the ED may further improve patient-centered outcome compare to the usual care (no TLT). Our central hypothesis is that TLT can be successfully initiated in a randomized study design in the ED.

**Impact:** We anticipate that introduction of TLT in the ED will lead to improved patient-centered utilization of intensive care for seriously ill older adult. If TLT is found to be feasible and acceptable in the ED, the potential exists to standardize the most challenging, in-the-moment decision-making for seriously ill older adults to improve their quality of end-of-life care nationally.

1. **SPECIFIC AIMS AND OBJECTIVES**

Aim 1: Determine the clinician-reported feasibility of conducting a clinician-level, randomized controlled trial of TLT compared to usual care in the ED.

Hypothesis: TLT is feasible to conduct a clinical-level randomized study in the ED.

Aim 2: Determine the patient-reported acceptability of TLT in the ED.

Hypothesis: The patients or surrogates (if patients are unable to consent) randomized to TLT will feel more heard and understood about their end-of-life care wishes (primary outcome).

1. **GENERAL DESCRIPTION OF THE STUDY DESIGN**

Overview

To demonstrate the feasibility (Aim 1) and acceptability (Aim 2) of TLT, we will conduct a parallel group, clinician-level, pilot randomized clinical trial among 40 emergency clinicians (~20 in TLT and ~20 in usual care) in the ED.

Randomization: Using REDCap’s integrated randomization module,^24^ we will conduct clinician-level randomization using random blocks of four to ensure that emergency clinicians are evenly distributed one-to-one between intervention and control arms.

**Aim 1: Feasibility**

We will conduct the randomized trial and measure the feasibility outcomes (e.g., time it takes to conduct the TLT conversations, see Outcomes below).

**Aim 2: Patient-Reported Acceptability**

Among the patients who were cared by the emergency clinicians enrolled in the randomized trial, we will measure the patient-reported acceptability of the TLT conversations (intervention arm only) and track their clinical outcomes via electronic health record (EHR) review (both intervention and control arms).

1. **SUBJECT SELECTION**

**Aim 1:** **Feasibility**

Emergency clinicians are subjects given they will answer few questions (i.e., clinician-reported feasibility questionnaire) after conducting the TLT conversations in the ED. Emergency clinicians will be randomized to intervention (TLT training) vs. usual care (no TLT training).

Inclusion: Attending physicians, resident physicians, or mid-level providers working in the ED who are willing to be randomized to become the study interventionists.

Exclusion: Emergency clinicians unwilling to consent and be randomized to intervention TLT training.

Recruitment: With the Chair’s approval and after reviewing the ED roster, the PI will announce the study in the staff meetings and solicit participation.

**Aim 2: Patient-reported Acceptability**

The subjects will be seriously ill older adults, or their surrogates being cared for by the participating emergency clinicians (both the intervention or control arms – see details on which outcome to be assessed for which arm in *6 Study Procedures, Outcome Assessment* below). If the emergency clinicians determine that the patient is not able to provide consent due to cognitive impairment, dementia, delirium, or critical illness, the surrogates will participate in the TLT conversations (Table 1).

Inclusion:

a. ≥50 years or older with ≥one serious life-limiting illness* being admitted to intensive care unit in the ED; or

b. ≥75 years or older being admitted to intensive care unit in the ED; or

c. ED clinicians will not be surprised if the patient died in the current hospital admission; and

d. English speaking

*Serious illness criteria with high one-year mortality were selected based on best practice recommendations^25^ similar to prior studies:^26-28^ 1) stage III/IV or metastatic cancer;^29, 30^ 2) end-stage renal disease on dialysis;^31^ 3) chronic heart/lung disease requiring home oxygen supplementation or experiencing shortness of breath with walking;^32, 33^ 4) moderate to severe dementia (surrogate required for enrollment); or 5) ≥2 hospitalizations in the past six months.^29, 34, 35^

Exclusion:

a. Unable or unwilling to provide informed consent; or

b. Non-English speaking; or

c. Clinically inappropriate, determined by emergency clinicians, and no surrogate is available

Recruitment:

| **Table 1. Intervention target and outcome assessment** | | |
| --- | --- | --- |
| **Ability to consent** | **Intervention target** | **Outcome assessment** |
| Present | Patient or surrogate (if patient unwilling due to critical illness) | Patient-reported acceptability + EHR |
| Absent | Surrogate | Surrogate-reported acceptability + EHR |

1. *How individuals are identified for recruitment including description of use of recruitment materials such as flyers, brochures, advertisements, letters, etc.*

🡪 In the ED, we will identify potential subjects by reviewing patients being cared for by the study interventionist clinicians from 8 AM to 10 PM, seven days per week using our EHR. No flyers, brochures, advertisements, or other promotional materials will be used.

🡪 Given the minimal risk of this study, our study team will provide a study information sheet for verbal consent.

1. *Who is responsible for identifying and recruiting individuals?*

🡪 Upon identification of potential subjects, our research team member (e.g., research assistant) will approach the interventionist emergency clinicians to see if his/her patient can be recruited for this study to confirm the inclusion/exclusion criteria.

1. *When and where individuals are recruited?*

🡪 Potential subjects will be recruited in the ED while receiving care.

🡪 After the intervention emergency clinician completes the TLT conversation, our research team member (e.g., research assistant) will approach the potential subjects or the surrogate for enrollment and completion of the patient-/surrogate-reported acceptability outcomes in the ED.

1. *How recruitment goals match the prevalence rates of the condition/disease being studied and the populations most impacted by the condition/disease being studied?*

🡪 We will recruit from all patients arriving in the ED, which will reflect the prevalence rates of seriously ill older adults in the ED.

1. *Methods to enhance enrollment of diverse individuals and under-represented populations*

🡪 We will cap enrollments of non-Hispanic Whites at 70% of the enrollment target and overenroll other under-represented minorities.

1. **SUBJECT ENROLLMENT**

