| Patient-reported acceptability of TLT conversation (primary outcome)* | A 5-point Likert scale (i.e., “How acceptable was it for your doctor to talk to you about your expectations for ICU care?” and “How likely would you recommend this conversation for other patients like you?” “Not at all (1)” to “Completely (5)”). | Immediately after the TLT conversation |
| Heard and understood | A National Quality Forum endorsed, validated measure for palliative care modified to fit the context of serious illness conversations (“How well they feel heard and understood by your emergency department clinician about medical care they would want if they were to get sicker?” a 5-point Likert scale “Not at all (1)” to “Completely (5)”).^39^ | Immediately after the TLT conversation |
| Patient-reported end-of-life quality of communication | A validated, quality of end-of-life communication survey (4 items selected a priori, a 10-point Likert scale “Worst you can imagine (0)” to “Best you can imagine (10)”).^40^ | Immediately after the TLT conversation |
| Decisional regret scale | A validated survey that measures “distress or remorse after a [health care] decision” (5 items, 5-point Likert scale “Strongly agree (1)” to “Strongly disagree (5)”).^41^ | After 24 hours, 48 hours, and 1 week |
| Clinical outcomes abstracted from EHR | Number of days to the first family meeting in intensive care unit (ICU), ICU length of stay (LOS), hospital LOS, # family meetings, ICU procedures (e.g., CPR, pressors, etc.), ICU mortality, hospital disposition, hospice utilization. | After discharge or upon patient death |

A research assistant blinded to treatment allocation will perform all follow-up assessments. Our team will extract data from the EHR using a standardized approach.^42^

Study Termination:

We will follow the participating clinicians for up to one year to accrue an adequate number of patients they admit to the intensive care unit. Given that an emergency clinician may encounter ~3 to 10 seriously ill older adults being admitted to the intensive care unit per month, we estimate that it would take approximately one year to accrue ~10 patient/interventionist ED clinician who might meet the inclusion/exclusion criteria for Aim 2. The follow-up assessments of the patients will terminate when/if the participants die or are discharged from the hospital.

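### Inclusion (c) carries neither the ICU-admission nor the age condition of (a) and (b), so the criteria permit patients outside the stated population; exclusion (a) also needs reconciling with the surrogate pathway

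*Protocol*

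**What the plan says.** The Protocol's Background gives the target: "We will conduct a pilot randomized trial of TLT on seriously ill older adults starting intensive care in the ED". Subject Selection, Aim 2, repeats it in part: "The subjects will be seriously ill older adults, or their surrogates being cared for by the participating emergency clinicians". Three alternative inclusion routes follow. The first sets an age, an illness and an ICU condition: "a. ≥50 years or older with ≥one serious life-limiting illness* being admitted to intensive care unit in the ED; or" The second drops the illness, raises the minimum age to 75 and keeps the ICU condition. The third has none of these and rests on a judgement: "c. ED clinicians will not be surprised if the patient died in the current hospital admission; and" Item (d) is English speaking. Under Study Termination, clinicians are followed for up to a year "to accrue an adequate number of patients they admit to the intensive care unit".

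On who decides, the recruitment text in Subject Selection has the research assistant go to the treating clinician to confirm the criteria. Clinicians are randomised to TLT training or none, so they know their arm. The only blinding stated is that of the research assistant who does the follow-up assessments.

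On consent, the first exclusion reads "a. Unable or unwilling to provide informed consent; or". The same section provides that, when the clinician finds the patient unable to consent, "the surrogates will participate in the TLT conversations (Table 1"). Table 1 has a row for absent ability to consent, with the surrogate as both target and reporter. The dementia item requires a surrogate, and the consent process under Subject Enrollment accepts consent from patient or surrogate.

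**The concern.** Two things are at stake.

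The first is who may be enrolled. The intervention is a conversation about a trial of intensive care, and its findings go to the intensivist. The acceptability question asks about expectations for ICU care. ICU length of stay, days to the first ICU family meeting and ICU mortality have no natural value for a patient who goes to a ward. A patient who enters by (c) without ICU admission therefore fits neither the intervention nor several of its outcomes.

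The second is comparability. Clinicians are randomised first and patients are selected afterwards. Route (c) is wholly a matter of judgement, and it is exercised by someone who knows the allocation. Only intervention clinicians receive the training (1 hour didactic + 4 hours communication = 5 hours) and $25 for each completed conversation; control clinicians receive a flat $100. The confirmation and consent steps are described only for interventionist clinicians, with no parallel step for control patients, although outcomes are collected in both arms. The pilot is also meant to supply the between-group difference and standard deviation for a full-scale trial, so any difference in case mix would carry forward.

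Exclusion (a) raises a smaller matter. It does not say whose inability or unwillingness counts, and staff could apply it in two ways.

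**Working it through.** The plan gives no figure to reproduce on this point. The check is of the logic of the criteria.

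**Conditions by route**

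| Route | Age | Serious illness | ICU admission | Clinician judgement |
| --- | --- | --- | --- | --- |
| (a) | ≥50 | required | required | no |
| (b) | ≥75 | no | required | no |
| (c) | none | none | none | required |

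**Grouping.** The list can be read as ((a) or (b) or (c)) and (d), or as (a) or (b) or ((c) and (d)). Neither gives (c) an age or ICU condition. English is secured in any case by the second exclusion.

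**Enumeration**, with English held true. Take ages 30, 60 and 80, serious illness yes/no, ICU admission yes/no, and the judgement in (c) yes/no: 3 × 2 × 2 × 2 = 24 profiles.

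- Meeting (c): 3 × 2 × 2 = 12.
- Meeting (a) or (b) but not (c): age 60 with illness and ICU (1), plus age 80 with ICU, with or without illness (2) = 3.
- Included: 12 + 3 = 15.
- Included through (c) alone: 12 − 3 = 9, because 3 of the 12 also meet (a) or (b).
- Included without ICU admission: 3 × 2 = 6, all through (c) alone.
- Included at age 30: 2 × 2 = 4, all through (c) alone.

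Crossing these with capacity (yes/no) and surrogate available (yes/no) multiplies each count by 4: 96 profiles, 60 included, 36 through (c) alone, 24 without ICU admission, 16 at age 30.

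**Exclusion (a).** Among the 60 included profiles, 60 ÷ 4 = 15 lack capacity and have a surrogate. If (a) refers to the patient's own consent, 0 of the 15 remain eligible. If it refers to consent by patient or surrogate, all 15 remain.

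These are counts of logical profiles, not proportions of patients. They show what the wording permits, not how often it would happen.

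**Outcomes exposed to a difference by arm.** In Table 2, conversation time and patient-reported acceptability, the two outcomes marked primary, are starred as intervention-arm only. Heard and understood, quality of communication, decisional regret, inpatient EHR documentation and the EHR clinical outcomes are unstarred and collected in both arms. Only this second group can be affected by a difference in case mix between arms. One caution: Specific Aims names heard and understood as the primary outcome for Aim 2 and words its hypothesis comparatively.

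**The case against.** The strongest reply is that the surrounding text makes the intention clear. The list is introduced as describing seriously ill older adults, the trial is for patients starting intensive care, accrual counts ICU admissions, and the acceptability question concerns ICU care. This stands as evidence of intent, and it limits the conclusion. A reader might infer that the enrolled population is not the stated one. The documents do not support that: the criteria permit a different population, and nothing shows that ward patients or younger patients are sought or how many would enter. The reply does not cure the wording, because screening staff apply the list.

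A second reply is that a shift in the (c) threshold is speculative, that clinicians knowing their arm is inherent in randomising them to training, and that clinician confirmation touches every criterion. All of this is fair. No document shows that training or payment moves the judgement. But (c) rests on judgement alone and so has the most room to move. A reader might also want to put a size on the resulting imbalance, or to say that it biases the outcomes Table 2 marks as primary. Any size would rest wholly on assumed inputs, and those outcomes have no control-arm comparison to bias.

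Third, a reader might infer that exclusion (a) removes the patients for whom the surrogate pathway exists. That follows only if (a) means the patient's own consent. The definition of subjects, Table 1, the dementia item and the consent process all point the other way. What remains is a conflict of wording.

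**Conclusion.** The point holds as a defect in the eligibility wording. Inclusion (c) is a stand-alone route without the ICU and age conditions of (a) and (b). It therefore permits English-speaking patients of any age, not going to the ICU, whose death this admission would not surprise the clinician. That is at odds with the stated population, the accrual basis, the acceptability question and the ICU outcomes.

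Uneven use of (c) by arm is possible, because the judgement is confirmed after randomisation by a clinician who knows their allocation. It would matter for the two-arm outcomes only. Its size cannot be stated: the protocol gives neither the share entering by (c) nor how their outcomes differ.

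Exclusion (a) needs a clarifying phrase; the protocol read as a whole does not bar surrogate enrolment. The conclusions rest on the list being applied as written. A statistical analysis plan could not repair this, since eligibility is fixed in the protocol.

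**What to change.** Restate inclusion as: being admitted to intensive care from the ED, AND English speaking, AND meeting (a), (b) or (c). The sponsor should reconcile the age range for (c) with its description of older adults and state the result.

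Record which route or routes each patient meets, in the same way in both arms, at the ICU decision and before any TLT conversation. This needs a screening step for control patients that matches the one for intervention patients.

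State that exclusion (a) applies when neither the patient nor, where the protocol allows one, a surrogate is able and willing to consent. Two shortcuts should be avoided. Letting any available surrogate stand in for any patient who declines would go beyond Table 1, which allows a surrogate for an unwilling patient with capacity only where critical illness is the reason. Merging (a) with exclusion (c) would lose the separate ground of clinical inappropriateness. Keep both limits.

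The cost is a short protocol amendment, one added field on the screening form and the matching control-arm step. Some patients who would have entered on judgement alone without ICU admission would be lost; the documents do not say how many.

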**Aim 1: Feasibility**

After introducing the study at staff meetings, the study team will obtain verbal, informed consent with a study information sheet.

**Aim 2: Patient-reported Acceptability**

Pre-screening: We will identify potentially eligible patients using the ED track board in the EHR.

Consent Process:

1. Upon completion of TLT conversation by the interventionist emergency clinician (who also provides clinical care for the patient), our study team (e.g., research assistant, PI) will obtain verbal, informed consent from the patient or surrogate (if applicable) in the ED.
2. The capacity to consent the patient or surrogate is determined by the interventionist emergency clinician who conducted the TLT conversation.
3. **STUDY PROCEDURES**

**Intervention:** Clinician-led conversations about patient’s values and goals, potential benefits and risks of intensive care, and anticipated outcomes are standard of care in the ED. TLT is a multi-modal intervention that provides patient-centered structures to this standard of care. In this evaluation of TLT in the ED, the intervention components will include: 1) a structured conversation guide; 2) clinician training to use the guide; 3) electronic health records (EHR) template for documentation; and 4) standardized communication with the intensivist (**Fig 1**).

1. The TLT Conversation Guide: The structured conversation guide entails discussing patients’ values and goals, prognosis, and shared decision-making to use a trial of intensive care. Originally used in ICU settings,^21, 22^ we systematically refined the guide to be used in the ED incorporating inputs from patient advisors’ and emergency clinicians’ inputs (Appendix).
2. Clinician Training: Leveraging the study team’s expertise in serious illness communication training, the clinician training will include a one-hour didactic on research methodologies and serious illness communication skills, followed by a four-hour communication training with trained actors. Similar training has been described previously.^36-38^
3. EHR Documentation: An Epic template for documenting the TLT conversation findings has been developed (Appendix).
4. **
[figure not shown]
**Intensivist Communication: A standard template to communicate the TLT conversation findings to the intensivists has been developed (Appendix).

Control Group: Emergency clinicians assigned to the control group will not receive the TLT training/guide. Patients cared for by the control group emergency clinicians will receive usual care in the ED. No restrictions will be placed on serious illness conversations in the control group.

Outcome Assessments: We will collect the following variables during and after the TLT conversations (Table 2).

For Aim 1 Feasibility, we will collect all outcomes from the intervention arm, and EHR outcome from both intervention and control arms.

For Aim 2 Patient-Reported Acceptability, we will collect all outcomes from both the intervention and control arms.

*For clarity, we placed * on outcomes only collected from the intervention arm.*

| **Table 2. Outcomes and Assessment Timing** | | |
| --- | --- | --- |
| **Aim 1: Feasibility (* indicates outcomes collected only from the intervention arm)** | | |
| **Outcomes** | **Descriptions** | **Timing** |
| Time to complete the TLT conversation (primary outcome)* | With direct observation, the study team will record how long it takes to complete the TLT conversation by the intervenist ED clinician. | At the time of TLT conversation |
| Intervention fidelity* | With direct observation, the study team will record the completion of TLT components using an intervention fidelity checklist. | At the time of TLT conversation |
| Clinician-reported feasibility* | The study team will ask the interventionist emergency clinician to complete two 5-point Likert scale questions (i.e., “How feasible was it to conduct the TLT conversation with your patient?” and “How likely would you recommend the TLT conversation for your colleagues?” “Not at all (1)” to “Completely (5)”). | Immediately after the TLT conversation |
| Recruitment* | The percent that agree to conduct TLT conversations | At enrollment |
| Clinician-reported satisfaction* | The study team will ask the interventionist emergency clinician to complete 5-point Likert scale questions (i.e., “How satisfied are you with the conversation? “Not at all (1)” to “Completely (5)”). | Immediately after the TLT conversation |
| EHR documentation by inpatient clinicians (i.e., intensivists) | Review EHR for new documentation of reference to TLT, serious illness conversation, change in code status, or advance directive forms by inpatient clinicians. | After 24 hours, 48 hours, and 1 week |
| **Am 2: Patient-Reported Acceptability (* indicates outcomes collected only from the intervention arm)** | | |
| **Outcomes** | **Descriptions** | **Timing** |
| Patient-reported acceptability of TLT conversation (primary outcome)* | A 5-point Likert scale (i.e., “How acceptable was it for your doctor to talk to you about your expectations for ICU care?” and “How likely would you recommend this conversation for other patients like you?” “Not at all (1)” to “Completely (5)”). | Immediately after the TLT conversation |
| Heard and understood | A National Quality Forum endorsed, validated measure for palliative care modified to fit the context of serious illness conversations (“How well they feel heard and understood by your emergency department clinician about medical care they would want if they were to get sicker?” a 5-point Likert scale “Not at all (1)” to “Completely (5)”).^39^ | Immediately after the TLT conversation |
| Patient-reported end-of-life quality of communication | A validated, quality of end-of-life communication survey (4 items selected a priori, a 10-point Likert scale “Worst you can imagine (0)” to “Best you can imagine (10)”).^40^ | Immediately after the TLT conversation |
| Decisional regret scale | A validated survey that measures “distress or remorse after a [health care] decision” (5 items, 5-point Likert scale “Strongly agree (1)” to “Strongly disagree (5)”).^41^ | After 24 hours, 48 hours, and 1 week |
| Clinical outcomes abstracted from EHR | Number of days to the first family meeting in intensive care unit (ICU), ICU length of stay (LOS), hospital LOS, # family meetings, ICU procedures (e.g., CPR, pressors, etc.), ICU mortality, hospital disposition, hospice utilization. | After discharge or upon patient death |

A research assistant blinded to treatment allocation will perform all follow-up assessments. Our team will extract data from the EHR using a standardized approach.^42^

Study Termination:

We will follow the participating clinicians for up to one year to accrue an adequate number of patients they admit to the intensive care unit. Given that an emergency clinician may encounter ~3 to 10 seriously ill older adults being admitted to the intensive care unit per month, we estimate that it would take approximately one year to accrue ~10 patient/interventionist ED clinician who might meet the inclusion/exclusion criteria for Aim 2. The follow-up assessments of the patients will terminate when/if the participants die or are discharged from the hospital.

Remuneration: For Aim 1 Feasibility, we will compensate $500 to clinicians randomized to the intervention arm for one-hour didactic and four-hour communication training. In addition, we will compensate $25 for every patient that the TLT conversation is completed. For control arm clinicians, we will compensate $100 after randomization. For Aim 2 Patient-reported Acceptability, we will compensate $20 for completing the surveys.

Data Sharing: We do not anticipate sharing the data with collaborators outside Mass General Brigham.

1. **RISKS AND DISCOMFORTS**

Compared to the usual clinical care, we do not anticipate any additional risks or discomforts to our clinician or patient participants other than privacy/confidentiality risks. Several steps have been taken to maximize privacy. Questionnaires will be completed in private, walled ED treatment areas. Subjects will be assured that refusal to participate will not affect their care in any way. Unique identification numbers will be assigned to participants to link contact information and study data. These identification numbers do not contain patient identifying information. All research personnel involved in any way in this project will complete training in the protection of human research subjects per guidelines issued by the U.S. Department of Health and Human Services, Office for Human Research Protection. Staff training conducted by the candidate will include information about the importance of confidentiality and techniques to maintain confidentiality of all information reported by research participants. All study data will be collected and stored using REDCap. The purpose is to provide a system and associated support resources to enable efficient and high-quality collection and management of research data that is standards-based in design, development, and implementation. Standard features of electronic clinical research data management systems are available in the web-based systems provided with the service. These include interactive data entry with real-time field validation, lab data imports, audit logs to record database modifications, database integrity checks, security (in logins, permissions based on need, and encryption), reporting, forms inventory, and exports to common statistical packages for analysis. The database system provides for secure web-based data entry with the data stored on servers that maintained by Mass General Brigham. The data is encrypted during transmission. Consistent with NIH guidelines, a Data Safety Monitoring Committee (DSMC) will not be required for this single site, interventional trial.

1. **BENEFITS**

No proven benefits to the participants are expected. However, we hope that providing patient-centered structures to the usual care will improve the alignment of intensive care utilization with patients’ values and goals.

1. **STATISTICAL ANALYSIS**

**Aim 1: Determine the feasibility of conducting a clinician-level, randomized controlled trial of TLT compared to usual care.**

Hypothesis: TLT is feasible to conduct a clinical-level randomized study in the ED.

Descriptive statistics will be used for baseline characteristics of the study sample. We will consider the feasibility threshold to be the following:

- The median time to complete TLT conversations is <10 minutes (primary outcome).

- >70% of intervention components are completed, assessed using intervention fidelity checklist by an observer/research team member.

- >70% of clinicians in the intervention group reporting “somewhat feasible (4)” or “completely feasible (5).

We will track recruitment, participation, and retention rates of interventionist clinicians, including reasons for not participating. We will track which inpatient clinicians authored the follow-up serious illness conversations in EHR. The EHR-based outcome will be assessed using a EHR review. We will publish our findings regardless of the results and will follow the CONSORT guidelines for reporting RCT.^43^

